### **1.2 Benefits and Risks**

The risks to participants are minimal with randomizing COVID-19 vaccination recommendations as part of clinical care, as it is simply testing two different vaccination strategies. The primary potential risk will be uveitis relapse. However, uveitis relapse is common and can be properly treated, and relapse related visual loss can be adequately and timely prevented provided a close monitoring. To minimize potential risk, we will implement best medical judgment and treatment if any study endpoint event occurs to assure the safety of participants.

The potential for public health benefit from our aims to randomize COVID-19 vaccination recommendations is of importance, potentially to the benefit of future

COVID-19 vaccination recommendation and decision in patients with uveitis. This study would provide direct evidence and timely data to guide physician to give proper recommendations on COVID-19 vaccination for patients with uveitis.

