## **5.5 Interventions**

Interventions will take place at the Baseline visit. The Primary Treating Ophthalmologist will provide the recommendation of COVID-19 vaccination to the subject according to randomization assignment. For those randomized to the prompt vaccination, subjects will be recommended to go to vaccination site and get COVID-19 vaccination as soon as possible. Our ophthalmologic clinic does not provide the vaccination service. We will only give the recommendation to patients. For those randomized to the deferred vaccination, subjects will be recommended to get COVID-19 vaccination after the remission of uveitis. **Remission is defined as an inactive disease for 3 months after discontinuing all treatments for eye disease.** At baseline, all patients will also be educated to immediately contact us by phone call once they experience any discomfort or have any new ocular symptoms of eye redness, eye pain, decreased vision, light sensitivity or fark, floating spots. We will ask questions as prespecified in **5.6 Follow-up** on the phone call.

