## **5.6 Follow-Up**

Routine follow-up encounters will then occur every month. Participants will complete trial visits primarily by telephone calls from the call center. However, all participants will need to complete an in-person clinic visit on the end of three months since baseline.

On phone call, patients will be asked to answer the following predetermined questions according to their randomization assignment. **Module 1** will be subjected to those in

prompt vaccination group, and **Module 2** will be subjected to those in deferred vaccination group.

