### **Module 1**

Question 1: Do you think you have had a uveitis worsening or disease recurrence (relapse) in the past month?

Yes, no or uncertain. If yes, specify which eye and duration.

Question 2: Have you ever experienced newly occurred eye redness in the past month?

Yes, no or uncertain. If yes, specify which eye and duration.

Question 3: Have you ever experienced newly occurred eye pain in the past month?

Yes, no or uncertain. If yes, specify which eye and duration.

Question 4: Have you ever experienced new blurred vision or decreased vision in the past month?

Yes, no or uncertain. If yes, specify which eye and duration.

Question 5: Have you ever experienced newly occurred light sensitivity in the past month?

Yes, no or uncertain. If yes, specify which eye and duration.

Question 6: Have you ever had newly occurred dark, floating spots in your field of vision (floaters, specks or moving clouds in your vision) in the past month?

Yes, no or uncertain. If yes, specify which eye and duration.

Question 7: Have you ever experienced other ocular or systemic symptoms in the past month?

Yes, no or uncertain. If yes, specify where and duration.

Question 8: Have you already been received any dose of COVID-19 vaccination?

Yes or no. If no, jump to Question 14.

Question 9: Which COVID-19 vaccine did you get?

Sinovac (CoronaVac), Sinopharm, ZFSW Biologics Company, others (specifically), or uncertain.

Question 10: How many doses of COVID-19 vaccines have you already been received?

One, two, three or more (specific numbers).

Question 11: When did you get each dose of COVID-19 vaccines?

Participants will be asked to provide the specific date as far as possible.

Question 12: Have you finished all required doses of COVID-19 vaccines?

Yes or no. If the answer is no, continue on Question 13, otherwise finished.

Question 13: When do you plan to get the next vaccine?

Participants will be asked to provide the specific date as far as possible. If participants answer they no longer intend to get the next vaccine, specific reasons should be provided. Questions finished.

Question 14: Why did not you get vaccinated?

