Patients will be asked to provide the reason for not having COVID-19 vaccination. Not willing to get vaccination, willing to get vaccination but having not yet gone to the vaccination site (specific reasons for not yet gone to the vaccination site required), having gone to the vaccination site but refused due to the lack of vaccines, having gone to the vaccination site but refused due to contraindication, other reasons (specifically). After completing this question, all participants will be encouraged to go to get vaccination as soon as possible on the phone, although they might have shown

their unwillingness to get one or they might have tried but failed.

At the end of phone call, if the patient answer yes to any of questions 1 to 7 in the Module 1, the patient will be instructed to come back to study site to complete in-person clinic visit for further evaluation and examination. Alternatively, the patient will also be allowed to go to local hospitals for evaluation and examination, but the patient need to send back the copies of all medical notes, records, laboratory or auxiliary examination reports from the local hospitals. **Participants will receive best medical judgment and proper treatment for worsening of the ocular or systemic conditions, including but not limited to step-up treatment, treatment interruptions even hospitalization. Nasopharyngeal swabs for RT-PCR testing of SARS-COV-2 will be performed on cases of hospitalization.** No matter where the evaluation is completed, patients will be instructed to undergo three mandatory ocular assessments, including **best-corrected visual acuity testing, slit-lamp biomicroscopy and ophthalmoscopy.** Mandatory materials send back from local hospitals include the medical record written by the attending doctor with signature and the prescription of that clinic visit. An adjudication committee who are unaware of group assignment will independently determine the endpoint according to these medical records from our study site or the local hospitals. **If clinically-confirmed uveitis worsening occurs, participants will be recommended to postpone subsequent vaccination until uveitis remission.**

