At the end of phone call, if the patient answer yes to any of questions 1 to 7 in the Module 2, the patient will be instructed to come back to study site to complete in-person clinic visit for further evaluation and examination. Alternatively, the patient will also be allowed to go to local hospitals for evaluation and examination, but the patient need to send back the copies of all medical notes, records, laboratory or auxiliary examination reports from the local hospitals. **Participants will receive best medical judgment and proper treatment for worsening of the ocular or systemic conditions, including but not limited to step-up treatment, treatment interruptions even hospitalization. Nasopharyngeal swabs for RT-PCR testing of SARS-COV-2 will be performed on cases of hospitalization.** No matter where the evaluation is completed, patients will be instructed to undergo three mandatory ocular assessments, including **best-corrected visual acuity testing, slit-lamp biomicroscopy and ophthalmoscopy.** Mandatory materials send back from local hospitals include the medical record written by the attending doctor with signature and the prescription of that clinic visit. An adjudication committee who are unaware of group assignment will independently determine the endpoint according to these medical records from our study site or the local hospitals. **If clinically-confirmed uveitis worsening occurs, participants will be recommended to postpone subsequent vaccination until uveitis remission. If a patient assigned to the deferred vaccination group is vaccinated without remission of his/her ocular disease, we will no longer provide any recommendations on vaccination and implement assigned intervention strategies, this patient will only be observed later.**

The vaccination records of all participants, including doses, times and vaccine types, will be verified at the Month 3 visit by seeking data from the Health Code System which has a linkage to databases of routinely collected individual-level vaccination information held by the Local Health Administrative Committee.

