### 6.2 Primary Outcome

The primary outcome will be the time to symptomatic worsening over the course of 3 months of follow-up.

**Symptomatic worsening is defined if one of following newly onset symptoms occurs in at least one eye lasting for at least 2 days: eye redness, eye pain, decreased vision, light sensitivity or floaters.**

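### An 'uncertain' answer to a symptom question leaves the call record without the eye and duration that the primary endpoint needs, and no rule says how it is coded

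*Supplement*

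**What the plan says.** **Call script (protocol 2.0, 5.6 Follow-Up).** Questions 2 to 6 of each module cover the five symptoms of the primary endpoint. Question 1 asks for the patient's own impression of worsening, and Question 7 about any other symptom. Questions 1 to 6 carry the instruction "Yes, no or uncertain. If yes, specify which eye and duration"; Question 7 does the same with location in place of eye.

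**Trigger for examination.** In the prompt group, "if the patient answer yes to any of questions 1 to 7 in the Module 1, the patient will be instructed to come back". The deferred group has the same rule: "if the patient answer yes to any of questions 1 to 7 in the Module 2, the patient will be instructed to come back". Neither module says what follows 'uncertain', and the SAP does not either.

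**Other contacts.** Months 1 and 2 are telephone calls, and "all participants will need to complete an in-person clinic visit on the end of three months since baseline". Section 5.5 adds that "all patients will also be educated to immediately contact us by phone call once they experience any discomfort", after which the same questions are asked. Section 5.7 allows unscheduled visits for any reason, with the module questions and three eye assessments.

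**Endpoint and analysis.** The primary event is one of five new symptoms in at least one eye "lasting for at least 2 days" (protocol 6.2, SAP 3.1). A masked committee decides from call records and medical records (SAP 3.1). Participants without an event are censored, and an event is dated to the Month 1, 2 or 3 encounter at which it is reported (SAP 10). Multiple imputation is a sensitivity analysis for those who withdraw or are lost before Month 3 (SAP 8 and 13).

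**The concern.** The script creates a third answer and gives it no consequence. A participant unsure at Month 1 about reduced vision or new floaters is not asked which eye or for how long, and those are the facts by which the committee tells an event from a non-event. Masked adjudication cannot restore facts that were never collected.

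Two things are at stake. If doubtful answers hide some real events equally in both arms, the trial loses events and power. If they do so unequally, the hazard ratio is biased. Unequal loss is possible because participants know which recommendation they received, the caller uses an arm-specific module, and the choice between 'yes' and 'uncertain' is subjective. The absent examination matters mainly for the secondary outcome of clinically-confirmed worsening, because the primary event rests on symptoms.

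**Working it through.** **1. What an 'uncertain' answer leaves behind**

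| Step | After 'yes' | After 'uncertain' |
|---|---|---|
| Eye recorded | yes | not asked |
| Duration recorded | yes | not asked |
| Examination prompted by the answer | yes | no |
| Facts needed for the primary event | present | absent |
| Coding rule in protocol or SAP | committee applies the definition | none stated |
| Covered by imputation if Month 3 is completed | not needed | no |

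SAP 10 has only two states, event and censored. A completer with an unresolved 'uncertain' is not shown to meet the definition and is not imputed, so censoring as event-free is the likely result. It is not the only possible one: protocol 9.2 limits the ITT set to patients whose primary outcome is available, while SAP 7.1 takes everyone randomized, so two analysts could differ.

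**2. Whether the next call repairs it**

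Questions 2 to 6 ask about symptoms that newly occurred in the past month. A doubtful symptom that began before the Month 1 call may fall outside the Month 2 question. If it is recovered there, SAP 10 dates the event to Month 2.

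**3. The plan's sample size, as a base for the power figures**

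Inputs (protocol 9.1, SAP 5): N = 1314, two-sided alpha 0.05, power 80%, HR 1.5, event-free proportion 0.90 in the deferred group, accrual in 3 of 6 periods, dropout 0.15. Assumptions: 0.90 applies at 3 months, survival is exponential, and a period is one month.

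- Events (Freedman): (1.960 + 0.842)² × (2.5/0.5)² = 7.849 × 25 = 196.2, so 197.
- Hazards: −ln(0.90)/3 = 0.0351 per month (deferred); × 1.5 = 0.0527 (prompt).
- Event probability with uniform accrual over 3 and study length 6: 1 − (e^(−3λ) − e^(−6λ))/(3λ) = 0.146 and 0.210, mean 0.178.
- N = 197/0.178 = 1107; /0.85 = 1302, against the stated 1314 (within 1%).
- Expected events at N = 1314: 1314 × 0.85 × 0.178 = 199.
- Power = Φ(√d × ln(1.5)/2 − 1.960); at d = 199, Φ(2.859 − 1.960) = 81.6%.

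**4. Equal loss in both arms (assumed shares of true events)**

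| Share lost | Events | Power |
|---|---|---|
| 0% | 199 | 81.6% |
| 5% | 189 | 79.6% |
| 10% | 179 | 77.4% |
| 20% | 159 | 72.5% |

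This base lets participants contribute up to 6 months at risk, whereas SAP 10 stops at Month 3. With 3 months each, expected events are 657 × 0.10 + 657 × (1 − 0.9^1.5) = 65.7 + 96.0 = 162 before dropout, or 137 after removing 15%, and starting power is 73% or 66%. That is a separate matter. A 20% loss then takes power to 64% or 57%, a drop of similar size.

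**5. Unequal loss (assumed 10% in one arm, 20% in the other)**

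Observed HR = ln(1 − p₁(1 − u₁)) / ln(1 − p₀(1 − u₀)), where p is the 3-month event probability and u the share lost (1 = prompt, 0 = deferred). p₀ = 0.10; p₁ = 0.10 if the true HR is 1.0, and 1 − 0.9^1.5 = 0.1462 if it is 1.5.

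| Lost, prompt / deferred | True HR 1.0 appears as | True HR 1.5 appears as |
|---|---|---|
| 10% / 20% | ln(0.91)/ln(0.92) = 1.13 | 1.69 |
| 20% / 10% | ln(0.92)/ln(0.91) = 0.88 | 1.32 |

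**The case against.** The strongest reply is that 'uncertain' is not a dead end. A 'yes' to any other of the seven questions on the same call leads to examination, and Questions 1 and 7 are broad. The questions are asked again at Month 2. With 30-day months and the ±7-day windows, that is 53 − 37 = 16 to 67 − 23 = 44 days after the Month 1 call. Patients are told to phone with any discomfort, and unscheduled visits include eye assessments. The committee also sees the whole call record and the Month 3 findings.

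This stands against a reading that a reader might reach, that doubtful flares go unexamined until Month 3. That describes only the scheduled examinations. It does not supply the missing rule: none of these routes is opened by the 'uncertain' answer itself, the patient's own call uses the same script, and an examination cannot show afterwards that a symptom lasted two days.

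A reader might also infer that 5.5 and 1.2 contradict the trigger. They do not. Section 5.5 governs calls that the patient starts. Section 1.2 says that "relapse related visual loss can be adequately and timely prevented provided a close monitoring", without defining that monitoring or tying it to each doubtful answer. There is tension, but no conflict.

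Finally, it is tempting to set assumed counts of 'uncertain' answers against the expected number of events. That would be sound only if every such answer hid a true event, and the plan states no event count. It is also fair that collecting more detail moves the subjective boundary to between 'uncertain' and 'no' and does not abolish it.

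**Conclusion.** The point holds as a gap in endpoint ascertainment. Followed as written, the script leaves the committee without eye and duration for any 'uncertain' answer, and nothing in the protocol or SAP says how to code it. That such participants end up censored as event-free is the probable consequence, not a stated rule, and applies only where no later contact resolves the answer.

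The size is unknown. At an assumed equal loss of 5% of true events the cost is 2 points of power; at 20% it is about 9. Bias in the hazard ratio needs loss that differs by arm, and neither its amount nor its direction can be read from the documents. The change is worth making because it is nearly free and the missing facts cannot be reliably recovered later.

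**What to change.** 1. In both modules, open the eye-and-duration item after 'yes' or 'uncertain' (for Question 7, location and duration), and mirror this in the eCRF.
2. Send these records to the masked committee, to classify each as event or no event under the existing definition, and say so in SAP 3.1.
3. Add to SAP 13 a sensitivity analysis of the primary outcome that counts 'uncertain' answers still unresolved after adjudication as events.
4. The investigators should decide, and write down, whether the existing post-symptom assessment applies to 'uncertain' answers. Its downside would be some additional visits with negative findings.

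Items 1 to 3 cost slightly longer calls, a little more adjudication and one further Cox model. They need no new staff or procedure.

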### 6.3 Secondary Outcomes

- a. Time to clinically-confirmed uveitis worsening.

**Clinically-confirmed uveitis worsening is defined if any of the following criteria are met in at least one eye: new active, inflammatory chorioretinal or retinal vascular lesions (determined by clinical examination such as ophthalmoscopy or ancillary testing such as fundus photography and fluorescein angiography); worsening of best corrected visual acuity by 0.3 LogMAR score or more; a two-step increase in anterior chamber cell grade relative to baseline; or a two-step increase in vitreous haze grade relative to baseline. A 2-step increase is represented by a change of grade 0 to grade 2+; or grade 0.5+ to grade 3+.**

- b. Proportion of each reason for symptomatic uveitis worsening.
- c. Proportion of symptomatic uveitis worsening.
- d. Proportion of each reason for clinically-confirmed uveitis worsening.

- e. Time to initiation of step-up treatment.

**Step-up treatment is defined if any of the following criteria are met: addition of another systemic immunosuppressive agent (or biologics), switching to another systemic immunosuppressive agent (or biologics), or increasing doses of any currently systemically administered drugs.**

- f. Time to treatment interruptions.

**Treatment interruptions are defined if any of the following criteria are met: decreasing doses of or discontinuing any currently systemically administered drugs due to adverse events rather than disease improvement.**

- g. Time to hospitalization for any reasons.
- h. Time to hospitalization for ocular disease.
- i. Time to laboratory-confirmed COVID-19.
- j. Patient adherence, defined as proportion correctly vaccinated for at least one dose or maintaining not vaccinated per protocol throughout the trial.
- k. Proportion of vaccinated type and dose.
- l. Proportion of uveitis remission throughout the trial.

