## **7 Adverse Events**

### **7.1 Adverse Event Reporting**

An adverse event (AE) is defined as any unfavorable medical occurrence in a subject who has ever received study intervention, regardless of a causal relationship with this intervention. Any worsening of a pre-existing condition or illness should be considered an adverse event. Worsening in severity of a reported adverse event should also be reported as a new adverse event. An elective surgery/procedure scheduled to occur during a study will not be considered an adverse event if the surgery/procedure is being performed for a pre-existing condition and the surgery/procedure has been pre-planned prior to study entry. However, if the pre-existing condition deteriorates unexpectedly during the study (e.g., surgery performed earlier than planned), then, the deterioration of the condition for which the elective surgery/procedure is being done will be considered an adverse event. For adverse events to be considered intermittent, the events must be of similar nature and severity.

The Investigator will monitor each subject for clinical and laboratory evidence of adverse events throughout the study. The Investigator will assess and record any adverse event in detail including the date of onset, event diagnosis (if known) or sign/symptom, severity, time course, duration and outcome, relationship of the adverse event to study intervention and any actions taken. All these information on non-serious and serious adverse events will be recorded at each study visit.

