## 11.2 Analytical Methods

- a. Time to clinically-confirmed uveitis worsening.

A proportional hazard model (univariate Cox regression) will be used to analyze the time to clinically-confirmed uveitis worsening.

- b. Proportion of each reason for symptomatic uveitis worsening.

Descriptive analysis will be used to report the proportions between groups. Difference between proportions as well as its associated 95% CI will be estimated with the Wilson score method.

- c. Proportion of symptomatic uveitis worsening.

Descriptive analysis will be used to report the proportions between groups. Difference between proportions as well as its associated 95% CI will be estimated with the Wilson score method.

- d. Proportion of each reason for clinically-confirmed uveitis worsening.

Descriptive analysis will be used to report the proportions between groups. Difference between proportions as well as its associated 95% CI will be estimated with the Wilson score method.

- e. Time to initiation of step-up treatment.

A proportional hazard model (univariate Cox regression) will be used to analyze the time to initiation of step-up treatment.

- f. Time to treatment interruptions.

A proportional hazard model (univariate Cox regression) will be used to analyze the time to treatment interruptions.

- g. Time to hospitalization for any reasons.

A proportional hazard model (univariate Cox regression) will be used to analyze

the time to hospitalization for any reasons.

- h. Time to hospitalization for ocular disease.

A proportional hazard model (univariate Cox regression) will be used to analyze the time to hospitalization for ocular disease.

- i. Time to laboratory-confirmed COVID-19.

A proportional hazard model (univariate Cox regression) will be used to analyze the time to laboratory-confirmed COVID-19.

- j. Patient adherence, defined as proportion correctly vaccinated for at least one dose or maintaining not vaccinated per protocol throughout the trial.

Descriptive analysis will be used to report the patient adherence between groups. Difference between proportions as well as its associated 95% CI will be estimated with the Wilson score method.

- k. Proportion of vaccinated type and dose.

Descriptive analysis will be used to report the proportion of vaccinated type and dose administered between groups. Difference between proportions as well as its associated 95% CI will be estimated with the Wilson score method.

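### Laboratory-confirmed COVID-19 has one planned test, a swab on hospitalisation, and no direct question in either phone module, so the outcome is probably under-counted and its active detection depends on admission

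*Supplement*

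**What the plan says.** Protocol 6.3 lists outcome i as "Time to laboratory-confirmed COVID-19". SAP 3.2 repeats it. Neither document adds a case definition, a testing schedule or a data source. SAP 11.2 gives the analysis: "A proportional hazard model (univariate Cox regression) will be used to analyze the time to laboratory-confirmed COVID-19".

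The one planned virus test is in Protocol 5.6, worded the same for both arms: "Nasopharyngeal swabs for RT-PCR testing of SARS-COV-2 will be performed on cases of hospitalization". The schedule in Protocol 5.10 has no swab or PCR row.

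The nearest telephone question, identical in both modules, is "Question 7: Have you ever experienced other ocular or systemic symptoms in the past month". A yes leads to an evaluation visit at which "patients will be instructed to undergo three mandatory ocular assessments, including best-corrected visual acuity testing, slit-lamp biomicroscopy and ophthalmoscopy". If the visit is at a local hospital, "the patient need to send back the copies of all medical notes, records, laboratory or auxiliary examination reports from the local hospitals".

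Two further provisions bear on the point. Protocol 7.1 says: "The Investigator will monitor each subject for clinical and laboratory evidence of adverse events throughout the study". For the Health Code System link, Protocol 5.6 says: "The vaccination records of all participants, including doses, times and vaccine types, will be verified at the Month 3 visit". It does not mention test results or infections.

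**The concern.** The outcome is defined broadly and looked for narrowly. A patient with a positive test who is never admitted is not asked about it directly at any contact. Under SAP 3.1 the adjudication committee works from call records and medical notes, so a test that nobody asked about may never reach it.

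The second issue is comparability. Admission for any reason and admission for ocular disease are outcomes g and h, compared between arms. Protocol 5.6 names hospitalisation as possible care for worsening, and SAP 4 hypothesises earlier worsening in the prompt arm. If admission differs by arm, so does the chance of being swabbed, and the Cox model for outcome i has no term for testing or admission.

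At stake is the trial's only infection outcome. Protocol 1.1 notes that vaccination may matter particularly in uveitis because these patients may be at higher risk from COVID-19. A count that reflects who was admitted would be a poor guide to that side of the question.

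**Working it through.** The documents state no COVID-19 incidence, admission rate or power for this outcome, so there is no planned figure to reproduce. The check is a reading of every route by which a case could enter, followed by an illustration on assumed inputs.

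**Routes of detection**

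- *Admission swab (Protocol 5.6).* Planned and active, in both arms, for hospitalised cases only.
- *Modules 1 and 2.* Questions 1 to 6 concern the eye. Question 7 is general. The rest concern vaccination and, in Module 2 Question 8, remission. None mentions infection, diagnosis or a test.
- *Calls the patient makes (Protocol 5.5).* Patients are told to phone about any discomfort, but the call uses the same questions.
- *Post-symptom and unscheduled visits (Protocol 5.6, 5.7, 5.10).* Three eye examinations are mandatory. Anything else is discretionary.
- *Local hospital papers (Protocol 5.6).* Laboratory reports are requested, but the mandatory items are the signed medical record and the prescription. No SARS-CoV-2 test is required.
- *Adverse event evaluation (Protocol 5.10, 7.1).* Made at every follow-up contact, with no virus test named.
- *Health Code System (Protocol 5.6).* Specified for vaccination records only.

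So one route is active and conditional on admission. The others are passive and depend on the patient volunteering the information or on a clinician choosing to test.

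**Illustration of the under-count by the swab alone**

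Inputs: 657 patients per arm (SAP 5); 3-month incidence and share of infections admitted and swabbed are assumed.

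Cases found per arm = 657 × incidence × P(admitted and swabbed | infected).

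- 1% incidence, 10% admitted: 657 × 0.01 = 6.6 true cases; 6.57 × 0.10 = 0.7 found.
- Lowest corner, 0.5% and 5%: 657 × 0.005 = 3.3 true; 3.285 × 0.05 = 0.2 found.
- Highest corner, 5% and 50%: 657 × 0.05 = 32.9 true; 32.85 × 0.50 = 16.4 found.

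These leave out the passive routes, whose yield cannot be estimated, so they are lower bounds on total capture under each assumption.

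**Illustration of the effect on the comparison**

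Observed rate ratio (prompt/deferred) = true rate ratio × [P(admitted | infected, prompt) ÷ P(admitted | infected, deferred)].

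Take an assumed true ratio of 0.50:

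- Admission ratio 1.5: 0.50 × 1.5 = 0.75.
- Admission ratio 2: 0.50 × 2 = 1.00.
- Admission ratio 1: 0.50 × 1 = 0.50, unbiased, with fewer cases counted.
- Admission ratio 0.5: 0.50 × 0.5 = 0.25.

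More eye-related admissions in the prompt arm would push the ratio up. Milder illness after vaccination, with fewer infected patients admitted, would push it down.

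**The case against.** The strongest reply is that planned testing is not the same as detection. Nothing restricts outcome i to the admission swab. Question 7 is asked monthly, a yes leads to evaluation, laboratory reports are requested, patients are told to phone about any discomfort, and adverse events are reviewed at each follow-up contact. A symptomatic outpatient case therefore has a way into the data. This stands: a reader might infer that COVID-19 is looked for solely in hospitalised patients, and the documents do not support that. What remains is that these routes are passive, and that asymptomatic or unreported cases can be missed.

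A reader might also infer that the comparison is tilted against prompt vaccination. The documents do not show this. The swab rule is identical in both arms, no admission rates are given, and the two mechanisms above act in opposite directions. The hazard ratio of 1.5 in the sample size section concerns symptomatic worsening and cannot be borrowed as an admission ratio.

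Nor do the documents call outcome i the sole measure of benefit. It is the only infection outcome, but hospitalisation for any reason could also carry COVID-19 admissions.

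Finally, limited testing suits a pragmatic trial followed mainly by telephone, and outcome i is one of 17 protocol secondary outcomes, which SAP 11.1 treats as descriptive. That limits the consequence. Unadjusted 95% confidence intervals will still be reported, however, and a descriptive estimate also needs ascertainment that readers can interpret.

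**Conclusion.** The point holds as a minor, cheaply improved weakness. The plan names any laboratory-confirmed case as the outcome, actively tests only on hospitalisation, and asks no direct question. Under-counting is probable. A distortion of the arm comparison is possible in either direction. Neither can be sized from the documents; every figure in the illustration rests on assumed incidence and admission probabilities. The primary outcome, the hypothesis test and the sample size are untouched.

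**What to change.** Add one question to Modules 1 and 2, in identical words, at every call and at the Month 3 visit: has the patient had any positive laboratory test for SARS-CoV-2 since the last contact, on what date, and can a copy of the report be sent? In the SAP, date the event by the positive test and report cases in each arm by route of detection (admission swab or outpatient report), so that detection tied to admission is visible.

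If the question is not added, state in the SAP and the report that outcome i captures cases found by admission swab or passive report only, and do not read it as overall infection incidence. Relabelling it as COVID-19 found at admission would not be accurate, because outpatient reports can also enter.

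The cost is a protocol amendment, one more question per contact and some effort to retrieve reports. No extra testing is needed. The question makes capture more complete and more even, but does not remove the dependence on who gets tested: an arm with more admissions would still be swabbed more, and outpatient testing could differ by arm in this open-label trial.
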